## Introduction

### Background

The transition to parenthood is a transformative period that requires physical, emotional, and social adjustments to new norms and expectations. While there is significant focus on the transition for birthing parents (persons with a uterus) [1], nonbirthing parents (parents who do not give birth, including fathers, sexual-minority parents, adoptive parents, or nongestational coparents) are less supported in the transition to parenthood [2,3]. Perinatal mental health and psychosocial adjustment challenges are common among both parents, which can have significant impacts on parenting relationships and child outcomes [4,5]. Higher parenting self-efficacy, defined as a parent’s perception of their ability to execute tasks associated with raising a child [6], has been associated with improvement in many outcomes for both parents and children, including lower parental anxiety and depression and fewer behavioral problems in children [7]. Even in uncomplicated pregnancies and births, parents may struggle with developing their parenting self-efficacy [8] and report anxiety and depression symptoms [9-12]. Poor parental mental health is known to be comorbid and can adversely impact the interparental relationship, leading to relationship dysfunction and negatively impacting child outcomes [13]. By contrast, high parental self-efficacy in one parent is associated with higher parenting self-efficacy in the other [14]. Thus, it is essential to identify ways to support all parents during the early postpartum period to improve individual, couple, and family outcomes.

In Canada, recommendations for postnatal care vary by province, with no standardization of care, education, or support across the country [15]. In Nova Scotia, the recommendations for birthing parents are to have a comprehensive postpartum assessment with their health care provider at approximately 6 to 8 weeks after birth [15]. While there is focus on family-centered care, there are no specific follow-up recommendations for the nonbirthing parent, leading to a significant gap in support. Families should be offered postpartum depression screening at 2 weeks post partum, 6 to 8 weeks post partum, and 4 months post partum [15]. However, this does not always occur in practice [16].

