To address this need, our team developed and evaluated an SMS text messaging program, Essential Coaching for Every Mother, in which we demonstrated improved parenting self-efficacy and reduced postpartum anxiety in first-time birthing parents [24-26]. A limitation of the original program was that it focused only on birthing parents, excluding nonbirthing parents. Thus, we recently developed Essential Coaching for Every Partner to focus on nonbirthing parents, which complements the information provided in Essential Coaching for Every Mother by delivering evidence-based information directly to nonbirthing parents via SMS text messaging during the first 6 weeks of the postpartum period [27]. The Essential Coaching Postpartum program (inclusive of all types of parents) includes 6 weeks of evidence-based daily SMS text messages on topics such as infant care, normal development, parental mental health, and self-care and was designed in collaboration with parents and postpartum health care providers based on evidence-based information [28-31]. The goal of Essential Coaching Postpartum is not to replace face-to-face contact with health care providers but rather be an adjunct to standard care with specialized information targeting the unique needs of new parents. The aim of this study is to evaluate the effectiveness of Essential Coaching Postpartum on nonbirthing parents, birthing parents, and parent dyads in Nova Scotia.

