### Eligibility Criteria

Participants will be recruited prenatally and postnatally. To pre-enroll prenatally, eligible birthing parents will (1) be pregnant (>28 wk) with their first child, (2) understand English, (3) have a mobile phone with SMS text messaging functionality and a data plan, and (4) live in Nova Scotia. Eligible nonbirthing parents will (1) have a pregnant (>28 wk) partner (ie, the birthing parent) expecting their first child or will be expecting their first child via an alternative method (eg, adoption or surrogacy), (2) understand English, (3) have a mobile phone with SMS text messaging functionality and a data plan, and (4) live in Nova Scotia. Participants who pre-enroll prenatally will only be considered enrolled and assigned a study number once they text “birth” to the study mobile phone number and are randomly assigned.

To enroll postnatally, eligible birthing parents will (1) be early postpartum (<7 d) with their first child, (2) understand English, (3) have a mobile phone with SMS text messaging functionality and a data plan, and (4) live in Nova Scotia. Eligible nonbirthing parents will (1) be early postpartum (<7 d) with their first child, (2) understand English, (3) have a mobile phone with SMS text messaging functionality and a data plan, and (4) live in Nova Scotia.

Participants (both birthing and nonbirthing parents) will be excluded if they (1) have a newborn who dies or is expected to die before leaving the hospital; (2) have no access to a mobile phone, either personal or shared; (3) are unwilling to receive SMS text messages; (4) decline participation or withdraw; or (5) participated in a previous iteration of this project (eg, development or evaluation). Parents are not required to participate as dyads to be inclusive of all family compositions; however, involvement of the other parent, if applicable, will be encouraged. Participants who do not fully complete the baseline survey will be considered withdrawn from the study. If the participant was randomly assigned to the intervention, they will continue to receive the messages, but no further data will be collected from them.

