### Screening and Baseline

Interested participants will complete a standardized SMS text message script for the eligibility screening process. During prenatal screening, participants will be assessed for preliminary eligibility, and those who qualify will be asked to text the study mobile phone number within 7 days of giving birth to be enrolled. At this stage, participants will be encouraged to provide their partner’s mobile phone number, if applicable, so that the partner’s interest can be assessed. Once a birthing person gives birth or enrolls post partum, they will complete additional screening questions to confirm eligibility.

After the birth of their child, all interested participants will complete the postpartum eligibility and randomization processes. During this stage, additional information will be collected, including the newborn’s name, date of birth, and feeding preference (ie, breast or chest feeding, formula feeding, or combination feeding). Participants will then be randomly assigned to the intervention or control group and asked to complete the consent form and baseline survey. If a parent dyad is participating, the nonbirthing partner will be sent an SMS text message after randomization to indicate their preferred type of feeding messages and to complete the consent form and baseline survey. Linked parent dyads will always be placed in the same intervention group. If dyad members complete the screening process separately and are inadvertently assigned to different groups, both parents will be moved to the intervention group.

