### Intervention Group

Participants will receive the standard education provided at the hospital where they give birth. After enrollment, participants in the intervention group will receive messages until 6 weeks post partum. Birthing parents will receive Essential Coaching for Every Mother, and nonbirthing parents will receive Essential Coaching for Every Partner. Figure 1 provides examples of messages from each program. Messages are automatically scheduled according to the infant’s date of birth, beginning on the second evening after birth. Participants who enroll later will receive messages starting from their enrollment date (eg, someone who enrolls on day 5 will not receive messages from days 2-4). TextIt will be used to program and schedule the messages, and Twilio (Twilio Inc) [39] will serve as the secure gateway for sending and receiving messages. Participants are not restricted from seeking additional postpartum support outside of the study. They will continue to have access to standard perinatal care, including mental health services available through primary care providers and community resources.

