### Control Group

Participants will receive the standard education provided at the hospital in which they give birth. After enrollment, participants in the control group will not receive any Essential Coaching Postpartum SMS text messages. They are not restricted from seeking additional postpartum support outside of the study. They will continue to have access to standard perinatal care, including mental health services available through primary care providers and community resources. At enrollment, 6 weeks post partum, and 6 months post partum, participants will be sent an SMS text message with a link to complete the follow-up survey.

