### Data Analysis

Data will be analyzed on an intention-to-treat basis. Demographic characteristics, including parental age, marital status, educational level, and delivery method (eg, vaginal or cesarean), will be summarized using means and SDs or percentages, as applicable. Postnatal health care contacts for the parent and infant, health concerns, and feeding behavior will also be reported using means and SDs or percentages, as applicable. Any significant differences in baseline characteristics, assessed using chi-square tests or Mann-Whitney *U* tests, will be adjusted for in subsequent analyses. A *P* value of <.05 will be considered statistically significant for all outcomes.

For the primary and secondary outcomes, analysis of covariance will be used to determine whether scores differ between the 2 groups, with adjustments for pretest scores and any significant baseline characteristics. For the exploratory analysis, dyadic actor-partner interdependence multivariate multilevel modeling will be used to examine each dyad member’s relationship to primary and secondary outcomes after accounting for other explanatory variables. For implementation data, quantitative responses will be reported, and thematic analysis [48] will be conducted to describe participants’ experiences with Essential Coaching Postpartum.

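### Linked and solo parents are pooled in the primary ANCOVA with no pre-specified dyad-status term; the result is a programme-level effect for the enrolled mix and should be adjusted, split and worded that way

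*Protocol article*

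**What the plan says.** All references are to the protocol article.

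- **Who may enrol.** Eligibility Criteria: "Parents are not required to participate as dyads to be inclusive of all family compositions". The other parent's involvement is encouraged, and no quota or cap on dyads is given.
- **How dyads are allocated.** Screening and Baseline: "Linked parent dyads will always be placed in the same intervention group". If dyad members screen separately and are "inadvertently assigned to different groups, both parents will be moved to the intervention group".
- **What each arm receives.** Intervention Group: "Birthing parents will receive Essential Coaching for Every Mother, and nonbirthing parents will receive Essential Coaching for Every Partner". Control Group: "participants in the control group will not receive any Essential Coaching Postpartum SMS text messages".
- **What is compared.** Objectives sets the whole programme against standard care in all first-time nonbirthing parents (primary) and all first-time birthing parents (secondary). Dyads have a separate exploratory objective.
- **How it is analysed.** Data Analysis specifies intention to treat and an ANCOVA "with adjustments for pretest scores and any significant baseline characteristics". The baseline characteristics listed there do not include dyad status. Dyads are modelled only in the exploratory actor-partner analysis.

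**The concern.** For a solo nonbirthing parent, the arms differ by one stream in the household. For a linked one they differ by two, the second reaching the participant only through the partner. The Background gives reasons why this might matter for the primary outcome. Of the stream for birthing parents it says "we demonstrated improved parenting self-efficacy and reduced postpartum anxiety in first-time birthing parents", and it also says that "high parental self-efficacy in one parent is associated with higher parenting self-efficacy in the other". The Partner stream is recent, and Sample Size notes that no comparable evidence exists for nonbirthing parents.

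Two things are at stake. The first is interpretation: a positive primary result may be read as the effect of messages sent to the nonbirthing parent, when it averages over households with one stream and households with two. The second is balance: dyad status determines how a participant is allocated, and the rule for split dyads can make the dyad share differ between arms. Under the stated rule, dyad status enters the model only if a significance test happens to flag it.

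**Working it through.** **1. The plan's own figures, for scale.** Inputs from Sample Size: 4 Karitane points, 80% power, two-sided 0.05, 141 analysed, 15% attrition.

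- 141 / (1 − 0.15) = 165.9, rounded up to 166. The recruitment target is reproduced.
- The SD is not printed. Back-solving, SD = 4 × √(141/4) / (1.960 + 0.842) = 8.48. This is an implied value, not a stated one.

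**2. Streams reaching the participant's household.**

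| Nonbirthing parent | Intervention | Control |
|---|---|---|
| Solo | Partner stream | none |
| Linked | Partner stream on own phone, Mother stream on the partner's phone | none |

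**3. What the pooled contrast estimates when the mix is balanced.** With dyad share p, pooled effect = own-stream effect + p × spillover. The article gives no spillover size and no expected p, so these are illustrations only:

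- own 3, spillover 1, p = 0.2: 3 + 0.2 × 1 = 3.2 points
- own 3, spillover 1, p = 0.9: 3 + 0.9 × 1 = 3.9 points
- own 0, spillover 1, p = 0.9: 0 + 0.9 × 1 = 0.9 points
- spillover 0: the mix has no influence

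The share may also differ between the two parent types. At the reported count of 11 birthing and 5 nonbirthing parents, at most 5/11 = 45% of birthing parents could have been linked, while all 5 nonbirthing parents could have been.

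**4. Effect of the rule for split dyads on the mix.** Two independent 1:1 draws put both members in intervention with probability 1/4, split them with probability 1/2, and put both in control with probability 1/4. Moving split pairs to intervention gives 1/4 + 1/2 = 75% in intervention. Let p be the dyad share among nonbirthing parents and q the fraction of dyads screened separately. Assume moved parents are analysed in the arm they are moved to.

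- Dyads in intervention: p × (0.75q + 0.5(1 − q)). Dyads in control: p minus that. Solo parents in each arm: (1 − p)/2.
- p = 0.5, q = 0.25: intervention 0.28125 / (0.28125 + 0.25) = 52.9%; control 0.21875 / (0.21875 + 0.25) = 46.7%.
- p = 0.5, q = 1: intervention 0.375 / 0.625 = 60%; control 0.125 / 0.375 = 33%.
- q = 0: no imbalance at any p.

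**5. What that imbalance does to an unadjusted contrast.** Let g be the difference in 6-week score between linked and solo parents under standard care, after adjustment for the pretest score. The contrast then carries an extra g × (difference in dyad share). Per point of g this is 0.529 − 0.467 = 0.06 points in the first case and 0.600 − 0.333 = 0.27 in the second. The value of g is unknown.

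**6. Precision of a split by status.** Take 141 analysed, half linked, the implied SD and no gain from covariates. Each stratum then has 141/4 = 35.25 parents per arm.

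- SE of a stratum's arm difference: 8.48 × √(2/35.25) = 2.02, so a 95% interval of about ±4.0 points.
- Difference between strata: 2.02 × √2 = 2.86, so about ±5.6 points.

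The split can describe the data but cannot settle anything.

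**The case against.** The strongest reply is that the article never claims to isolate an own-stream effect. Objectives compares the programme with standard care, and Program Content and Design defines the programme as two related streams. On that reading, pooling is what a pragmatic comparison does. With concurrent 1:1 allocation the mix is balanced in expectation, so pooling alone blurs interpretation without biasing the estimate. This stands.

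A reader might go further and infer that linked parents receive a second treatment, or that a positive result could be produced by the partner's stream alone. The article does not support either. Each participant is sent one stream, and the statement about self-efficacy in couples is an association, not a treatment spillover. Even the assumed extreme case above (0.9 points, none of it own effect) would seldom reach significance: 2.80 × 0.9/4 = 0.63 standard errors, a power of roughly 10%.

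It is also fair to say that dyads are not ignored, given their own objective, hypotheses and model. That model cannot separate the streams, however, because arm is constant within a dyad. Nor would a solo-versus-linked split separate them. Status is not randomised, solo families may differ in structure or partner interest, and the linked nonbirthing partner consents only after randomisation.

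Finally, model covariates are often left to an analysis plan. Here, though, the article itself fixes the rule: adjust for a baseline characteristic only when it differs significantly. That rule is a poor basis for handling a factor that governs how participants are allocated.

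**Conclusion.** The point holds as one of adjustment, reporting and wording. It does not show that the primary comparison is invalid. With balanced allocation, the pooled estimate is a sound programme-level contrast for the mix that enrols; it cannot be read as the effect of the Partner stream alone. The same applies to the birthing-parent comparison and the Mother stream.

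The firmer reason to act is allocation. Under the split-dyad rule the dyad share can differ between arms, by about 6 percentage points (52.9% against 46.7%) or 27 (60% against 33%) in the two cases worked. These rest on an assumed 50% dyad share, independent 1:1 draws, and analysis in the arm moved to. If no dyads screen separately, the imbalance disappears. The sizes of any spillover and of any prognostic difference between linked and solo parents are not given and remain unknown.

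**What to change.** 1. At screening, before randomisation, ask every participant whether the other parent is enrolling or already enrolled, and record the answer. Whether a partner's number was supplied is not enough: it misclassifies partners who decline and pairs who screen separately.
2. Include this status as a pre-specified fixed factor in the nonbirthing-parent and birthing-parent ANCOVAs, regardless of baseline tests.
3. Report the 6-week Karitane arm difference for linked and for solo parents with intervals, labelled descriptive.
4. Word the primary conclusion as the effect of offering the programme to the enrolled parent(s), and do not let that wording depend on the solo estimate.

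The cost is one screening item, one model term and two descriptive estimates. The stratum estimates will be imprecise, non-randomised comparisons that cannot establish spillover. The factor adjusts for an unequal dyad share but does not undo the split-dyad rule itself: within linked pairs, those screened separately would still be over-represented in intervention. With 16 parents enrolled at the reported date, the item could still be introduced early.

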### Hypotheses

#### Primary Hypothesis

Our primary hypothesis is as follows: nonbirthing parents who receive Essential Coaching Postpartum will have higher parenting self-efficacy, better mental health (ie, lower scores for depression, anxiety, and stress), greater well-being (ie, lower distress scores and better sleep scores), and higher parenting outcomes (ie, higher relational satisfaction and coparenting) at 6 weeks post partum than those who receive standard care.

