### Randomization

Participants will be randomly assigned in a 1:1 ratio to either the intervention or control group using the TextIt platform’s “split randomly” function. This function distributes contacts equally across pathways, ensuring allocation to either the intervention or control condition. Randomization will occur only after a participant has given birth.

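### The one-way rule for discordant dyads makes allocation 3:1 among separately screened couples; its effect on the whole trial depends on how many such couples there are, which the article does not state

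*Protocol article*

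**What the plan says.** Under Randomization, the protocol article states: "Participants will be randomly assigned in a 1:1 ratio to either the intervention or control group". The split is made automatically by the messaging platform after the birth.

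Screening and Baseline deals with couples in two ways. For couples known to the study as such, "Linked parent dyads will always be placed in the same intervention group"; the nonbirthing partner is contacted after the randomisation and no later move is described. For couples not recognised in time, "If dyad members complete the screening process separately and are inadvertently assigned to different groups, both parents will be moved to the intervention group".

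Under Data Analysis, "Data will be analyzed on an intention-to-treat basis". The model is an analysis of covariance "with adjustments for pretest scores and any significant baseline characteristics". Enrolment route and dyad status are not named as covariates.

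The primary hypothesis concerns nonbirthing parents: "nonbirthing parents who receive Essential Coaching Postpartum will have higher parenting self-efficacy", compared with standard care at 6 weeks. Nonbirthing parents in discordant pairs therefore fall within the primary comparison.

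**The concern.** The rule runs in one direction. A parent who drew control moves to intervention if the partner later enrols separately and draws intervention. A parent who drew intervention can never move to control. The final arm then depends partly on whether both members of a couple came through screening on their own, which is a feature of the couple and not of chance.

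This does not sit with 1:1 assignment and intention-to-treat, whichever way the moved parents are analysed. If they count in the arm they were moved to, the groups are no longer those formed by randomisation. If they count in the arm they first drew, some controls received the programme and the contrast is diluted. The analysis can choose between these two costs but cannot remove both, because they come from the allocation rule itself. The primary (nonbirthing), secondary (birthing) and exploratory (dyad) comparisons all contain such parents.

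**Working it through.** **Inputs.** From Sample Size: 141 evaluable parents of each type, 15% attrition, a 4-point effect, 80% power and two-sided alpha of .05. From Randomization: 1:1. From Screening and Baseline: discordant pairs go to intervention. Not given: *s*, the number of nonbirthing parents in separately screened dyads. I assume 5, 20, 40 and 60 of 166. The low value is included because the article calls the mismatch inadvertent. I also assume that the two members' draws are independent.

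**The plan's own figure.** 141 / (1 − 0.15) = 165.9, rounded up to 166. This agrees with the article, and 1:1 gives 83:83.

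**Separately screened dyads.**
- Both draw intervention: 0.5 × 0.5 = 0.25
- Both draw control: 0.5 × 0.5 = 0.25
- Discordant: 1 − 0.25 − 0.25 = 0.50, all moved to intervention
- Final allocation: 0.25 + 0.50 = 0.75 against 0.25, i.e. 3:1

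A simulation of 200,000 pairs gave 0.750 in intervention and 0.501 discordant.

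**All nonbirthing parents, analysed as moved.** Everyone else stays 1:1, so intervention = (166 − s)/2 + 0.75s and control = (166 − s)/2 + 0.25s. The share of separately screened parents is 0.75s / intervention in one arm and 0.25s / control in the other.

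| s | Intervention : control | Share in intervention | Share in control | Difference |
|---|---|---|---|---|
| 5 | 84.25 : 81.75 | 4.5% | 1.5% | 0.03 |
| 20 | 88 : 78 | 17.0% | 6.4% | 0.11 |
| 40 | 93 : 73 | 32.3% | 13.7% | 0.19 |
| 60 | 98 : 68 | 45.9% | 22.1% | 0.24 |

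If separately screened parents differ from the others at 6 weeks by *D* points that the covariates do not capture, the bias is roughly the last column times *D*. The documents give neither the sign nor the size of *D*.

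**Analysed as first randomised.** The arms stay at 83:83 in expectation. Of the *s* parents, half draw control and half of those are moved, so 0.25s of the 83 controls are treated. The expected difference is 4 × (1 − 0.25s/83).

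The article states no SD. Solving its sample size for one gives 4 × √(70.5/2) / (1.96 + 0.84) ≈ 8.48, so the standard error of the difference is 8.48 × √(2/70.5) ≈ 1.43. Power is Φ(effect/1.43 − 1.96).

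| s | Controls treated | Diluted effect | Power |
|---|---|---|---|
| 5 | 1.25/83 = 1.5% | 3.94 | 79% |
| 20 | 5/83 = 6.0% | 3.76 | 75% |
| 40 | 10/83 = 12.0% | 3.52 | 69% |
| 60 | 15/83 = 18.1% | 3.28 | 63% |

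The power column rests on the back-solved SD and, like that back-calculation, takes no account of any gain from covariate adjustment.

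**Unequal arms alone** matter little. With 20% of parents separately screened (ratio 1.22:1), power for an undiluted 4 points is 79.6%.

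**The case against.** The best defence is that this is a fallback. The main pathway already gives a couple one allocation, and partners' numbers are sought at prenatal screening, so discordant pairs may be few. That stands. At 5 such parents the split is 84:82 and the dilution 0.06 points. A reader might infer from the 3:1 figure that the trial as a whole departs far from 1:1. The documents do not support that, since the ratio applies only to separately screened dyads.

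A reader might also infer that the rule inflates the treatment effect because couples who each enrol on their own are more engaged. With 40 such parents and a 4-point advantage, the unadjusted spurious difference would be 0.186 × 4 ≈ 0.74 points. But a gap as large as the whole planned effect has no basis in the article, and even its direction is unknown. The comparison pool also includes linked couples, in which both parents take part. The planned model adjusts for the pretest score, which would take up much of a stable difference in level. Only a residual difference would bias the result, and then only if parents are analysed as moved. Under the ordinary meaning of intention-to-treat the consequence is dilution, which is conservative.

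It is also fair to say that an article may leave the handling of reassigned participants to the full protocol or SAP. That silence is not the point here. The reassignment rule is stated outright, and either way of analysing its result has a cost.

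Finally, a symmetric rule has its own difficulty. A parent who has already received messages cannot be made unexposed. The remedy has to work mainly before the split.

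**Conclusion.** The point holds as a defect in the allocation rule. Given independent 1:1 draws, 75:25 among separately screened dyads follows exactly, and it conflicts with the stated 1:1 assignment and intention-to-treat analysis.

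The consequence for the primary comparison is conditional on a count that the article does not give. Over the assumed range of 5 to 60 nonbirthing parents it runs from negligible to material. Analysed as moved, there is a possible bias of unknown sign and size; analysed as randomised, up to about 0.7 of the planned 4 points is lost. The documents do not establish that the trial result will be biased, or in which direction. The rule is still worth replacing, because a symmetric one keeps couples together equally well.

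**What to change.** Replace the one-way rule with one allocation per family.

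- **Before the split.** Ask every contact, prenatal or postnatal, whether the other parent has enrolled, and for that parent's mobile number. A parent whose partner is already randomised skips the split and takes the partner's arm. The probability of intervention is then 0.5 for every dyad, and the expected split returns to 83:83.
- **Pairs still found discordant, and pairs already moved.** Analyse both parents in the arm of the parent randomised first, whatever messages were received. Record the order of randomisation so that the rule can be applied.
- **Reporting.** Give the number of such pairs and add a sensitivity analysis that leaves them out.

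The cost is one screening question and branch in the messaging flow and a few sentences in the protocol and SAP. Slight dilution remains from the few pairs in which messages had already begun. With 11 birthing and 5 nonbirthing parents enrolled by 15 September 2025, against targets of 166 each, nearly all allocation was still to come.
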